## Methods

### Study design

The study is a parallel, two-armed, superiority randomised controlled trial (RCT) that examined the effectiveness and uptake of online parent coaching combined with FF. The study is registered with the International Standard Randomised Controlled Trial Number registry (ISRCTN25513446). Data will be collected at baseline (pre-randomisation, T0), post-intervention (6-month post-randomisation, T1) and follow-up (12-month post-randomisation, T2).

### Study setting

The RCT will be conducted with families of children referred for assessment of loss of skills to the Developmental Regression Clinic at Monash Children’s Hospital in the Australian state of Victoria. The clinic is a public specialist tertiary service jointly funded by the hospital and a Medical Research Future Fund (MRFF) grant from the Australian government. Referrals are accepted from GPs or other medical specialists in Victoria. Eligibility for the clinic is based on suspected developmental regression, defined as parent- or clinician-reported loss of previously acquired skills in at least one developmental domain (communication, motor, social engagement or daily living) within the preceding 18 months. This is a clinical presentation rather than a discrete entity with a single diagnostic code, and it serves as the trigger for a structured multidisciplinary assessment to clarify the underlying aetiology. Regression is operationalised through detailed developmental history, supported where possible by documented prior functioning (eg, reports, home videos or clinician observations).

Children referred to the clinic are seen by a multidisciplinary team consisting of a paediatrician, an occupational therapist clinic coordinator, a neuropsychologist and/or a speech pathologist. Each child undergoes a comprehensive assessment consisting of parent-report, direct observation and standardised measures, with the specific assessment battery tailored to each child’s age, abilities and presenting features. The multidisciplinary team conducts weekly case conferences with neurology and genetic specialists to plan first-line investigations and early management. Children are reviewed at approximately 8 weeks, 6 months and 12 months. At each review, investigation results and clinical progression are reviewed, and further targeted investigations are recommended where an explanatory diagnosis remains unclear. Possible explanatory diagnoses considered include autism, neurodegenerative conditions (eg, Batten disease), developmental epileptic encephalopathies, recognised genetic conditions (eg, Rett syndrome), and other rare or emerging genomic or mitochondrial conditions, including possible phenotypic expansions. Where autistic features emerge over the follow-up period, an autism-focused assessment may be undertaken alongside standard developmental assessments and medical investigations. The clinic explicitly seeks to minimise diagnostic overshadowing by continuing to investigate other potential causes of regression even when autistic features are present.

### Eligibility criteria

Parents of children aged between 1 and 15 years with loss of skills in one or more developmental domains (communication, motor, social engagement or daily living) within the 18 months prior to their first visit to the Developmental Regression clinic are the target population. Other eligibility criteria include residency in Victoria, Australia, comfort in reading English at Grade 7 level, access to an internet-enabled device and an active email account.

Participants are not eligible if: (1) the child’s history of loss of skills cannot be corroborated through developmental surveillance information, clinical assessment or review of video/audio recordings, or (2) the regression is judged to have occurred primarily in the context of significant environmental adversity such as documented abuse, neglect or severe household adversity or (3) the child’s condition warrants prioritisation of medical intervention and stabilisation over research participation.

### Recruitment

Eligible parents of children who are currently attending, or have attended, the Developmental Regression clinic will be invited to participate in the study. The consent procedure includes the clinic/trial coordinator sharing and explaining to the parent using the appropriate information and consent forms (see online supplemental material for an example). The exact timing of the approach for research consent will be determined by consideration of the parent’s physical, cognitive and psychological capacity at the time, as well as the practicality of the circumstances, to ensure that obtaining informed consent is not burdened by high impact on time and other resources that could compromise care. Prospective participants will also be presented optional consent options, including those consenting their data to be recorded in a skill loss registry or shared with other registries. Participant enrolment will start in January 2026, and the last participant is expected to be enrolled in December 2026.

Participants can also nominate another carer of their child or a support person to access the FF programme. The additional carer or support person will be invited to give their own consent to create a login for the programme but will not be required to complete assessments that are expected of participants.

### Interventions

#### Family Focus

The FF programme was developed specifically for parents caring for children experiencing developmental regression. It is organised into a foundational knowledge and skill-building package consisting of 10 self-paced online modules, integrating a blend of text, images, interactive and auditory content. Six of these modules’ topics are also featured in podcast content.

All parent participants will receive their own login to access FF for the duration of the trial. To enhance programme engagement, nudges and reminders in the form of emails and text messages will be delivered based on parents’ preferences.

Importantly, the FF programme was constructively aligned with specific target behaviours that were expected to change and operationalised as parent outcomes. The programme was developed through a five-step co-design process. First, a review of the literature on family resilience and participation, parent stress, parent empowerment, and child outcomes identified parental stress and mental health as critical intervention targets given their high prevalence and demonstrated impact on family functioning, particularly in families of children with developmental disabilities.^2028 32^,^35^ Second, thematic mapping of the literature, lived experience inputs, and best-practice guidelines^36^,^39^ identified key protective and risk factors influencing family resilience and participation, resulting in five module domains: (1) parent mental health and support, (2) parent skill and family culture, (3) child development and participation, (4) community participation and (5) siblings and family. Third, module content, learning objectives and skill targets were systematically aligned with intended outcomes—including reductions in parental stress—through iterative forward and backward mapping. As part of the codesign consultation phase, parents with lived experience were also consulted about whether access to a coach with allied health training, in addition to an online module package, would provide added benefit and how such support could be delivered. Fourth, content was co-developed and reviewed by authors who are allied health professionals and by parents with lived experience, to ensure relevance and appropriateness. In the prototyping stage, parents with lived experience provided feedback on the layout and functionality of specific elements of the FF programme (eg, individual modules and dashboard functions) and the proposed coaching options (eg, focus, frequency and supporting features in the dashboard). Finally, the programme was delivered as an online package with a coaching component, informed by iterative feedback during the development process. See table 1 for an overview of the module domains and content.

**Table 1 T1:** Module domain, module title and brief outline of Family Focus online content

Domain	Title	Outline
1. Parent mental health and support	Module 1: Keeping yourself strong and healthy	Introduces the concepts of well-being and resilience, and explores what parents might experience when caring for a child with complex developmental needs
	Module 2: Being healthy and bringing support towards you and your family	Offers practical strategies to support parental mental health and well-being, including managing routines, bringing supports towards the family and engaging in health-promoting activities
2. Parent skill and family culture	Module 3: Building parenting skills to promote a healthy family culture	Explores ways that parents can help everyone in the family feel safe, secure and healthy, such as through family routines
	Module 4: The role of parents and ways to manage now and in the future	Considers the roles and responsibilities of a parent caring for a child with complex developmental needs, and presents practical resources for managing different challenges the family may face
3. Child development and participation	Module 5: Supporting your child’s participation at home	Introduces the meaning of participation and offers strategies to support a child’s participation in preferred activities
	Module 6: Supporting your child’s communication and social interaction	Supports parental reflection on their child’s needs and shares ideas for supporting their child’s communication and socialising at home
	Module 7: Supporting your child’s development in play, self-care and movement	Presents strategies to support a child’s development in the areas of play, self-care and movement including sensorimotor development
4. Community participation	Module 8: Being a part of the community and enjoying family life	Looks at common barriers families face in getting out and about, and explores ways families can stay connected with their communities
	Module 9: Making positive connections with old and new communities	Talks about the challenges families may face in participating in cultural and community activities and the strategies families can use to navigate these challenges
5. Siblings and family	Module 10: Supporting siblings and nurturing connections	Considers the needs of siblings of children with complex developmental needs, the impact and opportunities these challenges present, and shares ideas for offering support

The FF intervention provides educational resources and practical strategies targeting parent mental health, healthy behaviours (ie, sleep and physical activity) and the health, well-being and participation needs of all family members. Content focuses on building skills for managing caregiving responsibilities, establishing sustainable healthy home routines and supporting engagement in family and community activities. These components are designed to enhance parent empowerment and competencies, increase parental knowledge, skills and understanding to support adjustment to their child’s needs and caregiving requirements, while promoting the well-being of the whole family. Through these behaviour change targets, the programme aims to reduce parental stress as its primary, proximal outcome, recognising that lower stress is both a meaningful health outcome and a key pathway to improved child and family outcomes (see figure 1). As parents access support, resources and opportunities to build on their existing strengths, parents shape conditions that promote responsive caregiving, enhance their empowerment and knowledge around their child’s specific needs and decisions affecting their child and family, and support active engagement in activities that promote their own health and well-being, thereby reducing parental anxiety and depression (intermediate outcomes). Over time, these changes are expected to contribute to better child physical and mental health and an improved quality of life for the whole family (distal outcomes).

**Figure 1 F1:**
[figure not shown]
Theory of change.

In the intervention arm, FF is combined with coaching to augment these effects. Coaching offers guided goal setting, individualised problem solving and accountability over time. By providing tailored support and opportunities to apply and refine skills in parents’ real contexts, coaching is expected to strengthen key mechanisms of change.^13 14 29^ Consequently, FF plus coaching is hypothesised to produce greater and more sustained reductions in parental stress, larger gains in parent empowerment and well-being (intermediate outcomes) and, over time, more pronounced improvements in child participation, functioning and overall family quality of life (distal outcomes) compared with FF alone.

#### Coaching

Coaches will be allied health professionals with previous experience in coaching families of children with developmental differences in healthcare or disability settings. They will receive training on the FF programme content to ensure familiarity with the materials for parents. In addition, they will be trained on procedures such as booking of sessions, scope of the coach role and elements of sessions to be documented (eg, date, duration, parent goals and identified actions), as well as the principles underpinning the coaching model in this trial, which include:

Relationship based, collaborative and family centred.Goal generating, in line with the family’s needs, priorities, preferences and resources.Goals focused on overall child and family functioning, well-being or participation.Aiming to optimise empowerment and participation of the family as they provide support for their child with developmental regression and other family members.Coaching conducted in a strengths-based approach with joint planning, observation, reflection, action and feedback.

The role of the coach is to create opportunities for the parents to establish goals important to them and their family, reflect on what information and resources that would assist progress towards the goal, and to encourage parents to identify actions they can take. When parents identify goals that are related to content within the online programme, the coach will support reflection and discussion of the relevant online content and guide the parent to determine ways in which potential strategies can be implemented into family routines. Coaches will not provide direct therapy for the child and will recommend families consult with their community-based therapists for child-related therapy questions.

A fidelity checklist for the coaching approach will be developed and will include the expected coaching behaviours that reflect the key principles named above. Where the participant provides consent to audio-recording or video-recording, the coach will record the session to self-evaluate performance on the fidelity checklist post session. These recordings will be randomly sampled and rated by a research team member with experience in this coaching approach to ensure fidelity to the protocol and consistency across coaches in approach.

### Patient and public involvement

The FF programme was designed by bringing together perspectives and needs of parents and the expertise of researchers and clinicians from occupational therapy, speech pathology, psychology, developmental education, paediatric medicine and human-centred computing. Furthermore, family advocates from the Childhood Dementia Initiative are project partners, which ensures that the programme is relevant and acceptable to families of children with some of the most profound or complex forms of regression. Across a series of interviews and iterative workshops between 2023 and 2025, 14 families with lived and living experience played a significant role in identifying the target users’ needs, suggesting content topics, formats and features to include in the online programme and providing feedback on prototypes. Three additional parents of children with disabilities recruited from the community provided further insights and contributed to the development of podcast content that provide bite-sized, audio episodes on key topics. The author team of the FF programme content and this manuscript included a parent ([name]) with lived experience of caring for a child with developmental regression. Combining and triangulating systematic review findings^20 28^ with direct insights from families with lived experience has helped us create a programme that would resonate with and benefit its users.

The families who were involved in the codesign process will not be recruited to the current study. Details regarding the codesign process and findings will be communicated in a separate publication.

### Trial arms

#### FF arm

Parents in the comparison group will access the FF programme through an online portal but will not be able to request one-on-one coaching sessions. Instead, they will receive up to 12 prompts over 6 months (through SMS/email). The prompts will invite parents to think about the type of information or support that would be helpful to them and also suggest specific module content or other resources on the portal. These prompts will serve as a retention strategy and will support parents to navigate resources available in the online programme in the absence of a coach. Parents in this group will complete the same baseline, post-intervention and follow-up assessment as the intervention group.

#### Coaching+FF arm

Parents in the intervention group will access up to twelve 45-minute one-on-one coaching sessions via videoconference over a 6-month period, in addition to access to the FF programme. Parents will be offered flexibility with scheduling coaching sessions, which can occur weekly or at wider intervals to suit their needs and preferences. As the role of the coach in these sessions is to support the parent in identifying what they want to work on or change (the goal), parents are not required to have viewed a particular module or podcast in the programme before requesting a coaching session. After each coaching session, the parent is invited to complete a 4-item questionnaire to provide feedback on what is working well and identify areas for improvement in the sessions with their coach.

Participants and their children in both study arms may continue to receive any standard or necessary medical care as determined by their healthcare providers throughout the study period. Participants can discontinue their participation in the study at any point.

### Study procedures

#### Enrolment and randomisation

Eligible parents of children assessed through the research-embedded Developmental Regression clinic will be provided with information about the intervention trial and invited to participate. For those who consent to this study, if data on the outcome measures were collected as part of their first assessment or a follow-up review at the clinic within the past 6 months (whichever is closer to their study enrolment), the data will be transferred and used as their baseline data (T0) in the trial. Specifically, direct identifiers (eg, names) will be replaced by a code before participant data are transferred to a research-only database using REDCap, a secure, web application to support data capture.^40^ A 1:1 randomisation allocation sequence will be computer-generated within REDCap to allocate parent participants to the FF group or Coaching+FF group, thereby ensuring that participants, coaches, trial coordinator, outcome assessors and the research team analysing the data are concealed from the group assignment until baseline assessment and allocation are completed. Outcome assessors (clinicians completing assessments of the child) will remain blinded to group allocation across the assessment timepoints.

Participants will also complete post-intervention (T1) and follow-up (T2) assessments via online questionnaires hosted in REDCap. Figure 2 outlines the participant flow.

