#### Sample size

This study will enrol eligible families of children seen at Monash Children’s Developmental Regression Clinic who have consented to taking part in this intervention trial.

As there was a lack of available effect size estimates for interventions targeting families of children with regression, we used effect sizes from online interventions that aimed to improve mental health, stress and well-being of parents of children with a disability or chronic medical condition.^20^ To calculate the sample size required for *F-*tests (analysis of covariance (ANCOVA) and analysis of variance (ANOVA)), G*Power 3.1.9.7 software was used.^41^ To detect a large effect (*f*= 0.5) in the primary outcome (ie, parental stress) with a power of 80% and α of 0.05 (two-tailed), a sample size of 43 parents is required. To allow an attrition of approximately 30% between baseline (T0) and follow-up assessment (T2), a sample size of 56 parents (28 per group) is required.

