## Discussion

This study is the first to evaluate the effectiveness of an online programme with and without 1:1 health professional coaching, designed for families of children who have experienced developmental regression. The trial has several strengths including the pragmatic RCT design in which the trial is embedded within a routine clinical care environment. The blinding of healthcare providers collecting clinical data and outcome data helps to safeguard against potential bias. In addition, online coaching and the use of a flexible online platform to access the FF programme are expected to enhance accessibility. By integrating the insights from families with lived experience, advocates from lived experience agencies, and clinicians into the design of the programme and coaching approach, we have tried to ensure that the interventions are relevant to their needs and that potential risks or concerns are addressed in the design phase. Notwithstanding, given the clinical heterogeneity of the study’s population, it may be necessary to broaden the diversity of health service users (carers) who contributed their experiences and perspectives to the codesign of the online intervention. The additional features (eg, podcasts, audio files and videos) included in the FF programme may encourage engagement which will be measurable via the online portal. Together, these approaches will enable comparisons of the uptake and effectiveness of a self-guided programme for parents of children with developmental regression and a version of the programme that includes individualised coaching.

With this study being the first intervention trial for parents of children with developmental regression, we acknowledge limitations in relation to the study design. These include the lack of participant blinding to their treatment group, and the length and frequency of the follow-up assessments for capturing outcomes. Since baseline assessment may be conducted well before a participant begins accessing the programme or coaching, there is also a risk that variations in the time interval between the baseline assessment and the start of the intervention could allow external factors unrelated to the intervention to influence participants’ responses to intervention. Moreover, participants enrol in the trial one at a time, making it impractical to perform stratified randomisation. Nonetheless, we will conduct subgroup analyses where appropriate to explore potential variation in outcomes.

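### T0 may be a clinic score up to 6 months old, so the T0–T1 interval varies from about 6 to at least 12 months although the planned ANOVA treats T0 as one time point

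*Protocol article*

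**What the plan says.** Study design sets three time points: "Data will be collected at baseline (pre-randomisation, T0), post-intervention (6-month post-randomisation, T1"), with T2 at 12 months after randomisation.

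Enrolment and randomisation then lets existing clinic data stand in for a new baseline. Where outcome measures were taken at the first assessment or at a "follow-up review at the clinic within the past 6 months (whichever is closer to their study enrolment), the data will be transferred" and become T0. The rule is conditional: it applies only to parents who have such data, and it picks the score nearer to enrolment.

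Old scores are foreseeable. Recruitment invites "Eligible parents of children who are currently attending, or have attended, the Developmental Regression clinic", so past attenders are included. Study setting adds: "Children are reviewed at approximately 8 weeks, 6 months and 12 months".

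Data analysis plans a 2 (group) × 3 (time) repeated-measures ANOVA for the primary and secondary outcomes and names no baseline covariate. Aim and objectives also plans to explore the proportion of FF-group parents who move from above to below the clinical thresholds for stress, anxiety and depression by the end of the intervention.

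The Discussion lists the issue as a limitation: "Since baseline assessment may be conducted well before a participant begins accessing the programme or coaching", outside factors may influence how participants respond.

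**The concern.** The oldest permitted baseline precedes enrolment by as long as the intervention itself lasts. One parent's T0 may be days old and another's half a year old, yet both enter the ANOVA as the same level of Time. Two things are at stake.

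- **Precision.** The group-by-time contrast between T0 and T1 compares changes from baseline. It gains from a baseline that correlates well with T1 and loses from one that does not. Correlation between repeated stress scores may weaken as the gap grows.
- **Meaning of change.** The main effect of Time, and above all the single-arm threshold transitions, are read as change over the programme period. With an old T0 they also include whatever happened between the clinic visit and enrolment. Randomisation gives a single-arm figure no protection from this.

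**Working it through.** **Inputs from the Protocol article.** Age of T0 at enrolment: 0 to 6 months (Enrolment and randomisation). T1: 6 months after randomisation (Study design). Effect size f = 0.5, 80% power, two-sided alpha 0.05, 43 evaluable and 56 enrolled (Sample size). **Not given:** the T0–T1 correlation ρ and the share of parents with a reused score. Both are assumed below and varied.

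**1. The plan's own figure.** Sample size states the target "with a power of 80% and α of 0.05 (two-tailed), a sample size of 43 parents is required". With a noncentral F test and λ = f²N, numerator df 2, six cells (2 × 3) and one covariate give N = 43; other df = 2 variants give 42 or 43. Then 43 × 1.3 = 55.9, rounded to 56. The text states no baseline correlation, so neither figure visibly depends on the age of T0.

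**2. Interval.** Fresh score: 0 + 6 = about 6 months. Oldest permitted score: 6 + 6 = 12 months, plus any delay from enrolment to randomisation. Clinic reviews at about 8 weeks, 6 months and 12 months leave gaps of roughly 4 and 6 months between possible scores, so ages well above zero are plausible.

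**3. Variance of the T0–T1 contrast.** With equal SDs at T0 and T1, and relative to a comparison of T1 alone, the variance factor is 2(1 − ρ).

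| ρ | 2(1 − ρ) | Change from ρ = 0.6 |
|---|---|---|
| 0.6 | 0.8 | reference |
| 0.5 | 1.0 | 1.0/0.8 = 1.25, +25% |
| 0.4 | 1.2 | 1.2/0.8 = 1.50, +50% |

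Standard errors rise by √1.25 = 1.12 and √1.50 = 1.22, that is 12% and 22%. At ρ = 0.5 the factor is 1, so below 0.5 the contrast is less precise than T1 alone. If stress is stable and ρ stays at 0.6, there is no loss.

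**4. Dilution by the share affected.** Suppose a share p of parents have old scores with ρ = 0.4, the rest have ρ = 0.6, and mean change does not depend on score age. The average factor is 0.8(1 − p) + 1.2p = 0.8 + 0.4p. For p = 0.25 it is 0.9 (+12.5%), for p = 0.5 it is 1.0 (+25%), and for p = 1 it is 1.2 (+50%).

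**5. Power of that contrast.** For two equal groups d = 2f = 1.0, taken on the raw SD. Use a noncentral t with N = 43, 41 df and noncentrality d√N / (2√v), where v = 2(1 − ρ). Power is 0.947 at ρ = 0.6, 0.893 at 0.5, 0.832 at 0.4 and 0.772 at 0.3. T1 alone gives 0.893. On this reading power stays above 80% at ρ = 0.4 and is below it at 0.3.

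**6. Pre-post statements.** Observed T0–T1 change = change from clinic visit to enrolment + change from enrolment to T1. Only the second part belongs to the programme period. The first is zero by design only if T0 is taken at enrolment.

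**The case against.** The defence has several good points.

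- A reused clinic score is taken before allocation, so it fits the article's definition of T0. No common T0–T1 interval is promised, and there is no contradiction.
- Six months is a ceiling. The rule takes the nearer score and applies only where clinic data exist.
- The trial is pragmatic and embedded in a clinic, and its Recruitment section shows care about burden on families. Reusing clinic data is a declared trade-off, disclosed in the Discussion.
- Threshold transitions are exploratory. Even a fresh baseline leaves natural course and regression to the mean within an arm.

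All of this stands, and it limits the point. It does not remove it: disclosure changes nothing in the data, and the article states no shorter limit and no use of score age in the analysis. The subgroup analyses mentioned in the Discussion follow the remark on stratification and name no such factor.

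Some stronger readings are tempting but unsupported. A reader might infer that old baselines bias the arm comparison; they do not, because they precede allocation. A reader might infer that baseline adjustment loses much of its precision, or that the trial loses a large part of its effective sample. But the planned analysis is not a baseline-adjusted ANCOVA, which appears only in the sample-size text, and a large loss needs most scores to be old and a marked fall in ρ. A reader might also suppose that first-assessment scores reflect unusual distress at that visit; the article offers no evidence on stress scores at that time.

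**Conclusion.** The point holds as a matter of precision and interpretation, not of validity. T0 can be up to 6 months old at enrolment, so the T0–T1 interval varies from about 6 to at least 12 months while the ANOVA treats T0 as one occasion.

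The cost to the group-by-time contrast cannot be fixed from the article. If ρ fell from 0.6 for all parents, the variance would rise 25% (to 0.5) or 50% (to 0.4). The rise shrinks in proportion to the share of old scores and is near zero if stress is stable. These figures assume equal SDs at T0 and T1. They do not show that the trial misses its 80% power.

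The firmer consequence is for the Time effect and the FF-group threshold transitions, which would include pre-enrolment change. The limitation is acknowledged but not mitigated, and removing it for the primary outcome is cheap.

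**What to change.** Have every parent complete the DASS-21 in REDCap after consent and immediately before randomisation, and use it as T0 for stress and for the depression and anxiety scales. This also covers all three threshold-transition figures. Where clinic data are still reused for other scales, record the age of the score at randomisation and account for it in the analysis. Do the same for any parent already randomised on a reused DASS-21 score.

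The cost is 21 items, a few minutes per parent, and a minor amendment. No new system is needed, since T1 and T2 questionnaires already run in REDCap. Enrolment is planned from January to December 2026, so the change helps only parents not yet randomised when it takes effect.
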